### Sample size calculation

We propose to enroll 450 participants and have estimated 80% power to detect effects for our primary (alcohol use) and secondary (PrEP uptake) outcomes using formulas for longitudinal study designs with attrition [20]. Calculations assume an exchangeable covariance structure, measurements at baseline and 4 follow up points, and within-subject correlation among repeated measurements (rho) of 0.5. All estimates use two-sided tests of significance and alpha of 0.05. With a retention rate of 85% at 1 year, we would have > 80% power to detect effect sizes (Cohen’s d) of 0.23 (small effect size) [21] or greater for between-group comparison of continuous measures of alcohol consumption and other substance use. For binary outcomes (i.e. any binge drinking), we would have ≥80% power to detect differences in proportions of 10% or greater when the proportion in the control group ranges from 25 to 30%, using a repeated measures framework with 4 follow-up measures and assumptions stated above. Thus, this study is powered to detect small to medium effect sizes that are consistent with or smaller than others reported in the literature [22].

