## Methods/design

### Design

This study is an individually randomized controlled trial (RCT) of eSBI among youth vulnerable to HIV infection. Using an electronic portal, all participants are screened for alcohol misuse and receive immediate feedback regarding their level of use (e.g., how their use compares to others, whether it exceeds “safe use” guidelines); those who screen for moderate to high alcohol use, including binge drinking, are then randomized to either electronic intervention or control modules. All participants, regardless of randomization status, are followed for 12 months with in-person visits conducted at 1, 3, 6 and 12-month intervals (Fig. 1).

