### Identification and recruitment of participants

Youth are recruited from HIV testing centers at the three primary sites in Chicago: the Division of Adolescent Medicine at Lurie Children’s Hospital, Howard Brown Health, and the Village at the University of Chicago. Individuals are eligible if they are: (a) aged 16 to 25 years, (b) interested in testing for HIV infection and (c) HIV-negative or HIV status unknown (per self-report; verified at the point of HIV testing), and (d) are MSM or a transgender woman who has sex with men (i.e., born male, identify as female/transgender, and at any point in the gender transition process); (e) English-speaking.

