### Randomization

Upon enrollment, all participants complete HIV testing and screen for alcohol misuse using the Alcohol Use Disorders Identification Test (AUDIT) via an electronic portal, then receive immediate feedback regarding their level of use. Participants who screen moderate to high risk for alcohol misuse or endorse binge drinking on the AUDIT are randomized via computerized assignment in the portal (1:1) to either brief intervention modules to reduce alcohol misuse or a time-and attention-matched control (i.e., promotion of good nutrition). Study staff are blinded to random assignments.

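### The stated power reproduces with 450 people randomised, but the text makes 450 the number enrolled before alcohol screening; the article should say which it is and align the accrual target or the detectable effect

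*Protocol article*

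**What the plan says.** The eligibility list in the protocol article (Identification and recruitment of participants) covers age, interest in HIV testing, HIV status, population and language. It contains no alcohol criterion.

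The Randomization section gives the order of events: "Upon enrollment, all participants complete HIV testing and screen for alcohol misuse". It then says who goes on: "Participants who screen moderate to high risk for alcohol misuse or endorse binge drinking on the AUDIT are randomized". Allocation is 1:1. The Design section gives the same order: "those who screen for moderate to high alcohol use, including binge drinking, are then randomized to either electronic intervention or control modules". It adds "All participants, regardless of randomization status, are followed for 12 months", which has a purpose only if some participants are never randomised.

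The Sample size calculation section opens with "We propose to enroll 450 participants". It claims more than 80% power for d of 0.23 or more on continuous alcohol measures. For binary outcomes it claims at least 80% power for a 10-point difference when the control proportion is 25 to 30%. The one reduction it states is retention of 85% at one year. The article text gives neither an expected screen-positive fraction nor a separate target for the number randomised.

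**The concern.** In this article enrolment comes before the AUDIT, and the word participants includes people who are followed without being allocated to an arm. Those people add nothing to a comparison of the two arms. A power figure for that comparison has to rest on the number randomised, yet the only number given is described as enrolled.

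At stake is the point at which recruitment stops. A team that follows the text literally would stop at 450 enrolled and could randomise materially fewer. The power for the primary alcohol outcome would then be below the stated figure, and the Discussion's statement that the trial is large enough to detect an effect would rest on a sample that the written flow does not deliver.

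**Working it through.** **Inputs from the Sample size calculation section:** 450 people; 85% retained at one year; exchangeable within-subject correlation rho = 0.5; baseline and four follow-ups; two-sided alpha 0.05; 80% power. The 1:1 allocation is from the Randomization section. The fraction randomised, f, is not given and is treated as an assumption.

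**Step 1. Reproduce the stated continuous figure with f = 1.**

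- Variance factor for the mean of m = 4 follow-ups: (1 + (m − 1) × rho)/m = (1 + 3 × 0.5)/4 = 0.625. With rho = 0.5, the mean follow-up minus baseline gives the same factor: 0.625 + 1 − 2 × 0.5 = 0.625.
- Retained per arm: 450 × 0.85/2 = 191.25.
- Standard error in SD units: sqrt(2 × 0.625/191.25) = 0.0808.
- Detectable d: (1.96 + 0.8416) × 0.0808 = 0.2265, which rounds to the stated 0.23.
- Power at d = 0.23: Φ(0.23/0.0808 − 1.96) = 81.2%, which agrees with the stated figure of more than 80%.

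**Step 2. Reproduce the binary figures with f = 1.** The effective number per arm is 191.25/0.625 = 306. A reduction from 30% to 20% has 81.7% power, and one from 25% to 15% has 87.3%. Both meet the stated 80%.

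**Step 3. Find the number that must be randomised to keep 80% power at d = 0.23.**

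- Four measurements: n per arm = 2 × 0.625 × (1.96 + 0.8416)²/0.23² = 185.5. Dividing 2 × 185.5 by 0.85 gives about 437 in total, or 438 if n is first rounded up to 186. That is about 97% of 450.
- Five measurements (factor 0.6): about 420 in total, or about 93% of 450.

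**Step 4. Let f vary with 450 enrolled.** Detectable d = 0.2265/sqrt(f).

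| Assumed f | Randomised | Power at d = 0.23 | Detectable d | Power, 30% vs 20% | Power, 25% vs 15% | Enrolment needed to randomise 450 |
|---|---|---|---|---|---|---|
| 100% | 450 | 81% | 0.23 | 82% | 87% | 450 |
| 90% | 405 | 77% | 0.24 | 77.5% | 84% | 500 |
| 75% | 338 | 69% | 0.26 | 70% | 76.5% | 600 |
| 60% | 270 | 60% | 0.29 | 60% | 67% | 750 |
| 50% | 225 | 52% | 0.32 | 52% | 59% | 900 |

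**The case against.** The strongest reply is that the authors meant 450 randomised and used the word enrol loosely. The exact match at 450 supports this, because it is what a calculation based on 450 randomised would give. The CONSORT diagram, which could settle the matter, is not shown. This objection stands in full against a flat statement that the trial is underpowered. A reader might infer that from the flow described, but the article never says that accrual stops at 450 people screened, and it gives no screening yield.

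A second reply is that the power formula is cited and not written out, so 450 randomised is not the only set of inputs that would support the claim. This is partly right.

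- If dropout builds up to 15% at month 12 (assumed retention 98.75, 96.25, 92.5 and 85% at the four visits), about 384 randomised would keep 80% power at d = 0.23, which is 85% of 450.
- With baseline adjustment by ANCOVA (variance factor 0.625 − 0.5² = 0.375), about 262 would do, which is 58% of 450.

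With 450 randomised, however, these methods give a detectable d of about 0.21 and 0.175, and the article states 0.23. The simple calculation in Step 1 is the one that matches, and the binary sentence in the same section refers to four follow-up measures.

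A third reply is that an article condenses a longer protocol, so a screening yield may fairly be left out. That is so, and its absence is not the point. The point is that the target, the power statement and the participant flow that the article does print do not fit together as worded.

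Lastly, a detectable d of 0.32 could still be described as small to medium, which is how the section sums up its power. The broad conclusion could therefore survive even where the specific figure of 0.23 does not.

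**Conclusion.** The article has an internal inconsistency. Its power figures reproduce with 450 randomised, while its text defines 450 as the number enrolled before a screen that decides who is randomised. On the formula that reproduces the figures there is almost no slack: about 97% of those enrolled would have to be randomised, or about 93% if five measurements are counted.

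Whether power is actually lost depends on which number was meant. If 450 is the number randomised, the stated power stands and only the accrual target is misworded. If accrual stops at 450 enrolled, the stated power holds only if nearly all screen positive. Over an assumed range of 90% to 50% randomised, power at d = 0.23 would be 77% to 52%, and detectable d would be 0.24 to 0.32. That range is illustrative and has no source in the article. It also assumes four follow-up measurements, rho = 0.5 and 85% retention applied to all of them.

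**What to change.** In the Sample size calculation section, state which number 450 is.

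- **If it is the number randomised:** write that 450 will be randomised (225 per arm), make randomisation the accrual target, and give the larger number expected to be enrolled and screened. This would be 450 divided by the expected screen-positive fraction, for example 600 at an assumed 75%. The power figures stay as they are.
- **If it is everyone enrolled:** state the expected number randomised and its basis, restate the detectable effect as about 0.2265/sqrt(fraction randomised), and give matching power for the binary outcomes. The starting value should be the unrounded 0.2265, because 0.23 would overstate the result slightly.

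The first option costs a wording change and a plan for the larger number to be screened. The second costs a less favourable stated detectable effect and needs no extra participants.

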## Discussion

We describe herein the design of a randomized controlled trial of an eSBI, “Step Up, Test Up,” to reduce alcohol misuse among youth, ages 16–25 who are vulnerable to HIV infection in Chicago. The intervention draws on MI-informed approaches, including SBIRT, adapted in an electronic medium suitable for use in primary care and other generalist settings. We hope to extend the evidence base for eSBI to a group vulnerable to alcohol misuse, but with limited opportunity for intervention in traditional settings. We believe the design of this study has several strengths, including its focus on a younger group vulnerable to both alcohol misuse and related consequences, using a randomized controlled design in community-based practice environments where youth often seek testing for HIV infection. Furthermore, we believe that this intervention is developmentally responsive and addresses the age range with the steepest rise in both alcohol misuse and HIV acquisition (i.e, ages 16–25 years).

Step Up, Test Up, is among the first interventions to be tested in a rigorous trial of sufficient size to detect effects of eSBI and targeting youth who are vulnerable to alcohol misuse and HIV infection. We consider it a potential innovation in the HIV testing environment, which given the brief and electronic format, is well positioned for scale. It was designed to meet the standard for evidence-based interventions and to extend the base of evidence for intervention with this population with many assets, yet increased susceptibility to HIV and other STIs.

## Data Availability

Not applicable.

## Abbreviations

ARBA: AIDS Risk Behavior Assessment
AUDIT: Alcohol Use Disorders Identification Test
CASI: Computer Assisted Self Interviewing
CDC: Centers for Disease Control and Prevention
CES-D10: Center for Epidemiological Studies Depression 10-item Scale
CPSTF: Community Prevention Services Task Force
eSBI: Electronic Screening and Brief Intervention
GAD-7: Generalized Anxiety Disorder 7-item Scale
GEE: Generalized Estimating Equations
GLM: Generalized Linear Models
HIV: Human Immunodeficiency Virus
LEC: Life Events Checklist
MI: Motivational Interviewing
NIH: National Institutes of Health
PrEP: Pre-Exposure Prophylaxis
RCT: Randomized Controlled Trial
SBI: Screening & Brief Intervention
SBIRT: Screening, Brief Intervention & Referral to Treatment
US: United States
YMSM: Young Men Who Have Sex with Men
YTW: Young Transgender Women
